### Machine learning and predictive modeling

6.2

Beyond conventional regression, predictive modeling will employ a suite of algorithms, including penalized logistic regression (Elastic Net), decision trees, random forests, gradient boosting machines, support vector machines, and artificial neural networks. Two primary prediction tasks will be addressed: Early identification of neonates at risk of severe NARDS (OI > 16 within 72 h of diagnosis); Long-term prognosis (mortality, NDI, SRM, or growth restriction at the 24- and 36-month corrected age). Candidate predictors will be selected based on clinical relevance and temporal availability (within 24 h for early warning models; within 7 days for prognostic models). Feature selection and regularization will primarily use Elastic Net. To identify novel NARDS endotypes, Integrative Multi-Omics Factor Analysis (MOFA) or similar unsupervised data integration approaches [e.g., sparse Partial Least Squares Discriminant Analysis (sPLS-DA)] will be employed to identify latent factors and co-varying molecular pathways across omics layers. These integrated molecular signatures will subsequently serve as input features for downstream machine learning models (e.g., Random Forest) to construct highly discriminative and biologically informed predictive classifiers.

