### Model evaluation and validation

6.3

Model performance will be evaluated using the area under the receiver operating characteristic curve (AUROC), sensitivity, specificity, calibration plots, Brier score, and, where applicable, precision–recall curves for imbalanced outcomes. Internal validation will be performed using a robust strategy: randomly partitioning the cohort into a 70% Discovery Set and a 30% Internal Validation Set at baseline. The validation set will serve as an independent internal check for model generalizability. We will also perform internal validation using cross-validation and bootstrap resampling, strictly adhering to the TRIPOD reporting guidelines for predictive models (38). Where feasible, temporal or center-level external validation (or internal holdout by center) will be undertaken to assess generalizability.

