### Multi-omics integration and validation

6.4

Biomarker discovery will follow a split-sample design, with the cohort randomly divided into a training set (70%) and an independent validation set (30%). Within each omics layer, initial feature selection will be conducted using multivariate analytical techniques such as PLS-DA. Subsequently, integrative multi-omics analyses will be performed using the DIABLO framework (Data Integration Analysis for Biomarker Discovery using a Longitudinal Approach) to construct predictive models that integrate molecular and clinical data. Model performance will be evaluated in the validation set using AUROC, sensitivity, specificity, and calibration metrics, ensuring rigorous validation of biomarker-based classifiers.

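### Section 6.2 lists sPLS-DA, a supervised method that needs a class label, as an unsupervised route to novel endotypes, and names no label for it

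*Protocol article*

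**What the plan says.** Protocol article, section 6.2 (Machine learning and predictive modeling), states the purpose of the step and its first-named method: "To identify novel NARDS endotypes, Integrative Multi-Omics Factor Analysis (MOFA"). The alternative offered is "similar unsupervised data integration approaches [e.g., sparse Partial Least Squares Discriminant Analysis (sPLS-DA"). No class label is given for sPLS-DA, and the section does not say on which part of the cohort the step is fitted.

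The output is then used for prediction: "These integrated molecular signatures will subsequently serve as input features for downstream machine learning models (e.g., Random Forest"). The prediction tasks in the same section are "Early identification of neonates at risk of severe NARDS (OI > 16 within 72 h of diagnosis") and long-term prognosis at 24 and 36 months.

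Two later sections set the validation design. Section 6.3 plans "randomly partitioning the cohort into a 70% Discovery Set and a 30% Internal Validation Set at baseline", and adds cross-validation and bootstrap resampling. Section 6.4 says "Biomarker discovery will follow a split-sample design, with the cohort randomly divided into a training set (70%) and an independent validation set (30"%), and within that design "initial feature selection will be conducted using multivariate analytical techniques such as PLS-DA". Section 4.3 sets the target for the severe-NARDS signature at AUROC > 0.85.

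**The concern.** A discriminant analysis looks for the combination of features that best separates groups already known. It cannot start without the group label, so it is not an unsupervised method and cannot reveal groups that nobody has yet defined.

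Two things are at stake. The first is interpretation. If sPLS-DA is run with severe NARDS or another predicted outcome as its label, a report that the resulting endotypes differ in that outcome would be circular.

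The second is validation. The components become classifier inputs. A label-free step can be fitted on all infants without using their outcomes, but sPLS-DA cannot. If an analyst took the word unsupervised at face value and fitted sPLS-DA on the whole cohort, the outcomes of the hold-out infants would already be inside their features.

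**Working it through.** **1. The plan's own figures.** The protocol states no number for this step. Its only computed size, in section 3.6.2, is for the in-hospital mortality model: 10 events x 10 predictors = 100 events; 100 / 0.126 = 793.65, rounded up to 794. This reproduces. The same section supplies two inputs used below: the target of 1,000 infants and the 12.6% event rate.

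**2. Does sPLS-DA use the label?** For one component, with standardised features z and a 0/1 label y, the weight of feature j is w_j = sum over infants of z_ij (y_i - mean y). Weights are then shrunk so that only a chosen number stay non-zero, and the infant's score is the sum of w_j z_ij. Without y there is no w. The label unsupervised in section 6.2 is therefore wrong, whatever else the plan intends.

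**3. Which label could it be?** Section 6.2 names none for this step. The groupings it does name are the prediction targets: severe NARDS within 72 h, and the 24- and 36-month outcomes. A predicted outcome is the natural reading but is not stated.

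**4. What happens to the AUROC, by where the step is fitted?** A simulation used pure-noise features and an outcome unrelated to them, so the true AUROC is 0.50. It used one sPLS-DA component with soft-thresholded weights, 50 features kept, a 70/30 random split and 60 replicates per setting. For comparison, a label-free first principal component was fitted on all infants (10 replicates, so noisier). AUROC = (rank sum of cases - n1(n1+1)/2) / (n1 n0). The protocol does not give the feature counts (500, 2,000), the number kept, the event rates of 20% and 30%, or N = 300; these are assumptions. N = 300 stands for a smaller omics set, since section 3.8.2 makes biospecimens a voluntary sub-study with separate consent. The 12.6% is the protocol's mortality rate, used here as one possible event rate.

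| N | Features | Events | Fitted on all: hold-out | Fitted on 70%: hold-out | Fitted on 70%: apparent, in the 70% | Label-free, fitted on all: hold-out |
|---|---|---|---|---|---|---|
| 300 | 500 | 12.6% | 0.944 | 0.503 | 0.972 | 0.477 |
| 300 | 500 | 20% | 0.907 | 0.503 | 0.943 | 0.451 |
| 300 | 500 | 30% | 0.871 | 0.498 | 0.916 | 0.539 |
| 300 | 2,000 | 12.6% | 0.971 | 0.497 | 0.987 | 0.551 |
| 300 | 2,000 | 20% | 0.935 | 0.488 | 0.973 | 0.478 |
| 300 | 2,000 | 30% | 0.914 | 0.505 | 0.952 | 0.507 |
| 1,000 | 500 | 12.6% | 0.800 | 0.499 | 0.849 | 0.512 |
| 1,000 | 500 | 20% | 0.763 | 0.505 | 0.804 | 0.495 |
| 1,000 | 500 | 30% | 0.731 | 0.498 | 0.770 | 0.497 |
| 1,000 | 2,000 | 12.6% | 0.852 | 0.491 | 0.891 | 0.494 |
| 1,000 | 2,000 | 20% | 0.805 | 0.505 | 0.845 | 0.504 |
| 1,000 | 2,000 | 30% | 0.774 | 0.506 | 0.811 | 0.513 |

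A second simulation scored the top 50 noise features by covariance weight, with 20% events and 40 replicates per setting. Whole-cohort fitting gave 0.908 (N = 600, 2,000 features), 0.855 (1,000, 2,000) and 0.870 (1,000, 5,000); fitting in the 70% gave 0.50. At 1,000 infants and 2,000 features the two simulations give 0.805 and 0.855 for the same event rate, so the amount of inflation also depends on how the component is weighted.

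**5. Reading the results.** Whole-cohort sPLS-DA inflates the hold-out AUROC in every setting. Fitting in the 70% does not. A label-free component fitted on everyone shows no systematic inflation (0.45 to 0.55). The apparent column, 0.77 to 0.99, shows how optimistic the score looks on the infants whose labels built it. Cross-validation or bootstrap inside the discovery set was not simulated separately. It would share the problem if the component were built once beforehand, because each left-out infant's label would already have been used.

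**The case against.** The strongest reply is that the only error visible in the text is one word attached to one optional example. MOFA, which is label-free, is named first; sPLS-DA is a bracketed example after it, and if MOFA is used the problem does not arise. Section 6.2 lists methods and repeats the split for none of them, Elastic Net included. Sections 6.3 and 6.4 then set a 70/30 split, made at baseline in 6.3, and treat the 30% as independent. Using hold-out labels to build features would contradict that design. Where each step is fitted is also detail that a condensed article may leave to its analysis plan.

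Most of this stands, and it rules out three stronger readings that a reader might infer.

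- That the validation AUROC will be inflated, or that the 0.85 target could be met by noise under this plan. No section says the step is fitted on the whole cohort. Even if it were, the first simulation at 1,000 infants exceeds 0.85 in one of six settings, and then only at 0.852.
- That the endotypes would necessarily restate the outcome. This needs sPLS-DA to be chosen and its label to be the predicted outcome; the protocol states neither.
- That section 6.4 repeats the error. There PLS-DA is not called unsupervised, is used for feature selection and sits under the split.

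The reply does not remove the mislabel. That is a wrong statement about a named method, not a detail left out. It also leaves two gaps: section 6.2 does not tie this step to the discovery set, and the split does not by itself protect the cross-validation and bootstrap estimates that section 6.3 also plans.

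**Conclusion.** The point holds in a limited form. Section 6.2 assigns endotype discovery to a method that needs a known grouping, calls that method unsupervised, and names no grouping. This follows from the text and the definition of the method, and rests on no assumption.

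The consequence for the endotypes is conditional on sPLS-DA being chosen with a predicted outcome as its label. In that case its components cannot be reported as independently discovered endotypes.

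The consequence for the AUROC is conditional on the step seeing validation labels. If the split in 6.3 and 6.4 covers the step, the expected hold-out inflation is nil (0.49 to 0.51 on noise, true value 0.50). If it does not, the first simulation gives 0.73 to 0.85 at N = 1,000 and 0.87 to 0.97 at N = 300, under assumed feature counts, event rates and number of features kept. These figures illustrate whole-cohort fitting only. Resampling estimates would be optimistic unless the step is refitted in each resample.

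This is a small correction in wording, but it changes what the endotype analysis may conclude.

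**What to change.** - In section 6.2, remove sPLS-DA from the endotype step and use MOFA or another label-free method. Alternatively, keep sPLS-DA, call it supervised, name its class label, and do not call its components endotypes.
- State in 6.2 or 6.3 that every step that uses a label is fitted in the 70% discovery set only, applied unchanged to the 30%, and repeated within each cross-validation fold or bootstrap resample.
- Leave PLS-DA in section 6.4 as it is.

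The cost is a few sentences in the analysis plan. No extra data are needed. Refitting within resamples adds some computing time.

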### Model evaluation and validation

6.3

Model performance will be evaluated using the area under the receiver operating characteristic curve (AUROC), sensitivity, specificity, calibration plots, Brier score, and, where applicable, precision–recall curves for imbalanced outcomes. Internal validation will be performed using a robust strategy: randomly partitioning the cohort into a 70% Discovery Set and a 30% Internal Validation Set at baseline. The validation set will serve as an independent internal check for model generalizability. We will also perform internal validation using cross-validation and bootstrap resampling, strictly adhering to the TRIPOD reporting guidelines for predictive models (38). Where feasible, temporal or center-level external validation (or internal holdout by center) will be undertaken to assess generalizability.

### Multi-omics integration and validation

6.4

Biomarker discovery will follow a split-sample design, with the cohort randomly divided into a training set (70%) and an independent validation set (30%). Within each omics layer, initial feature selection will be conducted using multivariate analytical techniques such as PLS-DA. Subsequently, integrative multi-omics analyses will be performed using the DIABLO framework (Data Integration Analysis for Biomarker Discovery using a Longitudinal Approach) to construct predictive models that integrate molecular and clinical data. Model performance will be evaluated in the validation set using AUROC, sensitivity, specificity, and calibration metrics, ensuring rigorous validation of biomarker-based classifiers.

### Control of confounding and subgroup analyses

6.5

Multivariable models will adjust for key covariates (gestational age in completed weeks, birth weight z-score, sex, major comorbidities). We will perform stratified analyses by gestational age (<32 weeks, 32–36 weeks, ≥37 weeks) and present both adjusted and stratified effect estimates. To address prematurity as a potential source of confounding and misclassification (NRDS vs. NARDS), the central adjudication committee will review all ambiguous preterm cases, evaluating the timing of respiratory failure onset, radiographic features, surfactant exposure/response, and clinical course. For non-randomized treatment comparisons (e.g., ventilation strategies, surfactant use), we will use propensity score methods (matching, inverse probability weighting) and, when appropriate, instrumental variable approaches to reduce treatment selection bias. Sensitivity analyses will include restriction to term infants and to preterm strata to evaluate effect modification by prematurity.

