### Study design and setting

3.1

The SZ-NARDS registry is a prospective, multicenter, observational cohort study, scheduled to run from January 1, 2025, to December 31, 2028. This study will be conducted across nine tertiary-level NICUs in Shenzhen, China, selected for their infrastructure, expertise in neonatal critical care, and patient volume to represent a broad spectrum of care in the region. The study protocol is reported in accordance with the Strengthening the Reporting of Observational Studies in Epidemiology (STROBE) guidelines (30) (Supplementary Material 1). An overview of the study design is provided in Figure 1.

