**Figure 1 F1:**
[figure not shown]
Flow chart of the study design, the SZ-NARDS, 2025-2028. Neonates diagnosed with ARDS were enrolled as participants, with clinical measurements and biological specimens collected on day 1, during the acute exacerbation phase (defined by the peak OI), on day 28, and within 24 h before death or initiation of ECMO. Outcome data, including censored cases, will be finalized in 2028 after completing follow-up through clinic visits or phone calls. ARDS, acute respiratory distress syndrome; ECMO, extracorporeal membrane oxygenation; SZ-NARDS, the Shenzhen neonatal acute respiratory distress cohort study; OI, oxygenation index.

Clinical management of patients will remain at the discretion of the local attending physicians according to institutional guidelines, with no study-specific interventions. The study features an open design, allowing for the potential inclusion of additional centers that meet the established criteria during the recruitment period.

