### Statistical analysis plan

6.1

Continuous variables will be summarized as mean ± standard deviation (SD) or median with interquartile range (IQR), depending on distribution. Categorical variables will be presented as frequencies and percentages. Group comparisons will be conducted using the student's *t*-test or Mann–Whitney *U* test for continuous variables, and the *χ*² test or Fisher's exact test for categorical variables.

Univariate logistic regression will be used to examine associations between NARDS and study outcomes. Multivariable logistic regression will then be performed to identify independent predictors. Missing data will be addressed primarily using multiple imputation by chained equations (MICE), assuming data are missing at random. Variables with excessive missingness will be excluded according to predefined thresholds, and the imputation model will be structured accordingly. Sensitivity analyses will include complete-case analysis, k-nearest neighbors (k-NN) imputation, and inverse probability weighting to evaluate the robustness of findings to loss to follow-up. A two-sided *p* < 0.05 will be considered statistically significant. All analyses and visualizations will be conducted using R software (version 4.3.3).

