While innovative, our study has limitations. A primary limitation is the potential for significant selection bias, as the study is confined to Shenzhen, a single, economically developed “special economic zone” in China. The healthcare resources, patient demographics, and socioeconomic status in this region are not representative of the broader diversity across China, including rural or less developed areas. This may result in a study cohort with better outcomes than the national average, and therefore, our findings must be interpreted with caution and require validation in more geographically and socioeconomically diverse populations before they can be generalized. Loss to follow-up is another concern in longitudinal work. We have instituted multiple strategies to minimize dropout and will address any residual missing data with modern statistical methods like multiple imputation and inverse probability weighting, accompanied by sensitivity analyses. While the multicenter nature of the study introduces heterogeneity in clinical management, this is also a methodological opportunity. By meticulously documenting variations in interventions (e.g., ventilation strategies, surfactant use), we can leverage advanced statistical methods, such as propensity score matching or inverse probability weighting, to conduct comparative effectiveness analyses in a real-world setting. This can generate valuable hypotheses for future randomized controlled trials.

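### The stated adjustment set leaves out centre, although care follows each unit's own guidelines and that variation is to feed the treatment comparisons

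*Protocol article*

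**What the plan says.** Section 6.5, which deals with control of confounding, names the adjustment set: "Multivariable models will adjust for key covariates (gestational age in completed weeks, birth weight z-score, sex, major comorbidities". All four items describe the infant. For non-randomised treatment comparisons, with ventilation strategies and surfactant use as examples, the same section adds: "we will use propensity score methods (matching, inverse probability weighting) and, when appropriate, instrumental variable approaches to reduce treatment selection bias". It lists no propensity covariates and names no instrument.

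Section 6.1 gives t, Mann–Whitney, chi-square and Fisher tests, then univariate logistic regression, and continues: "Multivariable logistic regression will then be performed to identify independent predictors". No part of the article mentions a centre covariate, centre strata, within-centre matching, a random effect, generalised estimating equations or cluster-robust standard errors.

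On the setting, section 3.1 says: "This study will be conducted across nine tertiary-level NICUs in Shenzhen, China". On care, it says: "Clinical management of patients will remain at the discretion of the local attending physicians according to institutional guidelines, with no study-specific interventions". The Discussion accepts the consequence and treats it as useful: "While the multicenter nature of the study introduces heterogeneity in clinical management, this is also a methodological opportunity". The remedy it names is propensity matching or weighting.

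Centre has one analytic role. Section 6.3 allows, where feasible, validation of the prediction models across centres or with a centre held out.

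**The concern.** By the article's own account, which infant gets which treatment depends partly on the unit. The unit may also affect the outcome. The primary in-hospital outcome (section 4.1) includes requirement for ECMO, and Table 1 records ECMO capability, high-frequency ventilation, cardiac surgery and respiratory therapists as unit characteristics. A variable that influences both treatment and outcome belongs in the adjustment set, and infant-level covariates cannot stand in for unmeasured differences between units.

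Two things are at stake. A difference between hospitals could be reported as a treatment effect. Its confidence interval could also be too narrow, because infants in the same unit share that unit's risk. The Introduction offers management strategy as one possible explanation of the regional mortality difference that the study sets out to explain, so estimates of this kind bear on a stated aim.

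**Working it through.** **The plan's own figures (section 3.6.2).** Ten events for each of 10 predictors is 100 deaths. 100 / 0.126 = 793.7, rounded up to 794, which agrees with the article. At the target of 1,000 infants, 1,000 × 0.126 = 126 expected deaths. Over nine units the mean is 1,000 / 9 = 111 infants per unit.

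**Assumption.** The article gives no intracluster correlation (ICC), so a range is used. With a centre standard deviation s on the logit scale, ICC = s² / (s² + 3.29):
- s = 0.2: 0.04 / 3.33 = 0.012
- s = 0.4: 0.16 / 3.45 = 0.046
- s = 0.6: 0.36 / 3.65 = 0.099

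**Simulation of an infant-level treatment with no true effect.** Nine centres, a true odds ratio of 1, a test at two-sided 0.05, and logistic models with and without centre fixed effects.
- Set A: 111 infants per centre, about 12% mortality, 800 to 1,000 datasets per setting. The centre standard deviation of treatment log-odds runs from 1 to 3.
- Set B: 1,000 infants, 400 datasets per setting, treatment standard deviation fixed at 1. The outcome logit is −2.1 + centre effect + 0.5 × g, where g is an infant-level covariate that is also in both fitted models. The correlation ρ between a centre's treatment preference and its outcome risk is 0 or 0.5.

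False-positive rates without centre in the model:

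| ICC | Set A, treatment SD 1–3 | Set B, ρ = 0 | Set B, ρ = 0.5 (mean OR) |
|---|---|---|---|
| 0.012 | 6.6%–7.3% | 5.25% | 6.75% (1.09) |
| 0.046 | 9.0%–16.8% | 7.25% | 14.0% (1.16) |
| 0.099 | 12.6%–26.6% | 14.5% | 24.0% (1.23) |

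With centre fixed effects, set A gives 4% to 7%. Set B gives 4.0%, 4.25% and 7.75% at ρ = 0, and 4.0%, 4.25% and 5.25% at ρ = 0.5, with mean odds ratios of 0.98 to 1.01. With 400 datasets the Monte Carlo standard error at 5% is √(0.05 × 0.95 / 400) = 1.1 percentage points, so single cells are approximate.

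**Reading the table.** At ρ = 0 the mean odds ratio without centre stays at about 1.00, so the excess errors come from intervals that are too narrow. At ρ = 0.5 the estimate itself is also biased, by 9% to 23% on the odds-ratio scale. Centre fixed effects deal with both.

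**Parameter count.** Nine centres as fixed effects add eight terms. On top of 10 predictors that is 18: 126 / 18 = 7.0 deaths per parameter, or 100 / 18 = 5.6 at the minimum event count.

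**The case against.** The strongest reply is that this is a condensed article. Section 6.6 refers to an approved analysis plan that is not shown, and propensity covariates and variance estimators are commonly left to such a plan. That stands for the propensity scores. A reader might infer that the propensity models omit centre, but section 6.5 lists no propensity covariates, so centre is unnamed there and not excluded. The reply does not cover the multivariable models, whose adjustment set the article does state.

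A reader might also take it as established that the effects are confounded by centre. Confounding needs centres to differ in residual risk as well as in treatment. All nine units are tertiary units in one city, physicians keep discretion within each unit, and the article gives no figure for differences in risk. The risk is real but not demonstrated.

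A third inference would be that every interval is too narrow. For covariates that vary mainly within centres, such as sex or gestational age, ignoring clustering need not narrow intervals much. Large inflation belongs to exposures set by the unit. For those, set A's false-positive rate without centre is about 11%, 26% and 40% at the three ICCs, and the design effect 1 + (111.1 − 1) × ICC is 2.1 at 0.01 and 6.5 at 0.05. The article collects unit characteristics but plans no test of one, so these figures do not measure a planned analysis.

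The upper end for infant-level treatments is also demanding. A treatment standard deviation of 3 on the logit scale, with mean use of 50%, puts about a third of centres outside 5% to 95% use. Finally, treatment comparisons are not among the listed objectives, and the Discussion presents them as hypothesis-generating. That limits the stakes but does not make the list adequate.

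**Conclusion.** The point holds for the association and treatment-effect models. The stated adjustment set lacks a variable that the article itself makes a determinant of treatment, and the stated methods assume independent infants. Nothing else in the plan supplies the adjustment: centre holdout serves only the prediction models, and instrumental variables are optional with no instrument named.

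Under an assumed ICC of 0.01 to 0.10, the false-positive rate for an infant-level treatment is about 5% to 27% without centre and about 4% to 8% with centre fixed effects. The position within the first range depends on how strongly treatment use varies between centres and how far it tracks centre risk. At an ICC near 0.01 the error is close to nominal, about 5% to 7%.

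The documents do not support saying that treatment effects will certainly be confounded, that the propensity models leave centre out, or that unit-level error rates of 26% to 40% apply to any planned test.

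**What to change.** In section 6.5:
- Add centre to the adjustment set of the association and treatment-effect models, as a random intercept or, for treatment comparisons, as fixed effects or strata.
- State that propensity scores will include centre or be matched within centre.
- If any unit-level exposure is tested, use small-sample cluster inference for nine units (for example, a t reference with about 7 degrees of freedom).
- If an instrumental-variable analysis would use centre preference as the instrument, specify it separately, because fixed centre effects remove that variation.

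Leave the prediction models without a centre term, since a new centre's intercept is unknown, and keep the centre holdout of section 6.3.

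No new data are needed, because each centre already has an identifier (section 5.1). The choice should be fixed before analysis so that it cannot depend on results. The price is wider intervals, little information on treatments used uniformly within a centre and, with fixed effects, up to eight extra parameters against about 126 expected deaths. In a model that already carries 10 covariates, that falls below the article's own criterion of 10 events per predictor if the criterion is applied there. A random intercept avoids the eight fixed terms where treatment comparison is not the aim.
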